### Other assessments

2.19

Identification of how and why participants are “lost to follow‐up.”Measures taken to obtain the information if visits or data collection time points are missed.

If an assessment visit is missed, the CI will book another appointment, preferably within 1 week of the original date.
Outcome data that will be recorded from protocol nonadherers.

As far as possible, all outcome data will be collected for all participants, regardless of whether or not they have adhered to the protocol to enable intention‐to‐treat (ITT) analysis.

### Randomization

2.20

Initially, participants will be numbered in the order in which they give written consent. It is expected that recruitment will proceed gradually throughout the 3‐month window, therefore randomization by minimization will be undertaken during the recruitment process to either the HH4P or the usual care control group. The inclusion of a control group will allow home‐based HIIT utility evaluation by exploring changes in outcomes with the most robust, internally valid methodology available. The randomization procedure will be programmed before any participant recruitment into “Minim” MS‐DOS minimization software, to include a 1:1 ratio and group stratification by disease severity and gender. Upon recruitment of each participant and following their baseline assessments, randomized group allocation will be undertaken by a third member of the ST ([name]), blinded to assessment results. Following this, an email will be sent by [name] to the CI to notify them of each participant's allocated group; the CI will then notify the participant at the initial home visit.

### Blinding

2.21

Participants are unable to be blinded due to the nature of the exercise intervention. Similarly, the CI is unable to be blinded. However, initial baseline assessments for each participant will be undertaken before randomization, and the member of the ST ([name]) undertaking postintervention outcome assessments will be blinded to the participants' allocated group. All assessments will be undertaken in visits arranged independently of any intervention sessions, and away from the participant's home. Every effort will be made throughout to ensure these assessments are blinded, for example, by reminding participants not to discuss their group allocation with the blinded member of the ST. The final unblinding of the ST member who undertook assessments will be after the creation of a locked data set and analysis has been undertaken.

### Interventions

2.22

HH4P (HIIT + usual care).

The HH4P program is a 12‐week, thrice weekly HIIT program with the emphasis on providing options to facilitate individual preference, ability, and disease stage. As previously described in detail,^11^ HIIT sessions will comprise four sets of three 45 s bouts of high‐intensity exercise (≥75% HR_max_), with each bout interspersed with 15 s of rest. A 2‐min rest period will follow each set. HIIT sessions will last for 32 min each including warm‐up and cool‐down periods. Participants will choose from a range of exercises and will be supported by both physical and online resources.
Usual care control group

All participants allocated to this group will continue to receive their usual clinical care; thus, with the exception of the trial assessments they will not be asked to attend any additional visits or sessions.

Both the HIIT and control group will be asked to not begin additional structured physiotherapy or exercise sessions, or undertake contemporaneous interventional studies.

### Management of adverse and serious adverse events

2.23

The adverse event (AE) risks of taking part in this trial have been assessed to be low. However, all participants will be asked to report any new or worsening problems that they perceive to be related to participation in activity and/or exercise, as well as any relapses in their diaries. During fortnightly check‐ins, the CI will overtly request any information regarding AE's. These will then be recorded on the AE report form and reported by the CI to the ST. AE's considered related to the trial intervention will be followed until resolution or the event is considered stable. It will be left to the judgment of the CI, ST, and TSC, whether or not an AE is of sufficient severity to necessitate the participant to withdraw from the HH4P intervention.

Any serious adverse event (SAE), whether thought to be related to any trial intervention or not, will be reported by the CI to the ST within 24 h of the CI becoming aware of it. If the CI and ST consider that the SAE is not, or is unlikely to be, related to the trial, they will obtain a second assessment of causality from the TSC. SAE's which in the opinion of either adjudicator are possibly related to the trial intervention and unexpected will be reported by the CI to the Faculty of Health Research Ethics and Integrity Committee (FoHREIC) and Health Research Authority/Research Ethics Committee (HRA REC) within 15 days of having become aware of the event.

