### Feasibility outcomes

2.12

Measures of adherence and engagement:
Program completion (Objective Aiii)

Program completion will be defined as the percentage of participants that completed the 12‐week program of exercise or usual care, from those that underwent initial randomization.

Attendance at online group sessions (Objective Aii)Frequency and duration of exercise sessions (Objective Aii)Web‐based participant heart rate (HR) monitoring (Objective Aii)

Engagement in the home‐based program (exercise choice, HIIT session frequency, and duration) will be monitored based on exercise diary data recorded by the participant over the 12‐week program. Adherence will also be monitored through continual observation of online HR data (see below) and through attendance at online group meetings.

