### Safety

2.14

Adverse effects and events (Objective Ai; also refer to Section 2.23)

Adverse effects and events will be the primary measure of safety, which will contribute to the assessment of the practicality of HIIT in the remotely supervised home setting. Adverse effects and events will be patient recorded in participant diaries throughout the 12‐week program, and reported to the CI during fortnightly online drop‐ins.

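### The diary request screens adverse events by the participant's own attribution to exercise, and the text does not secure equal prompting in the two arms.

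*Protocol article*

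**What the plan says.** All references are to the protocol article.

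- **Role of AEs (Section 2.14).** "Adverse effects and events will be the primary measure of safety". They are recorded in participant diaries during the 12 weeks and "reported to the CI during fortnightly online drop‐ins".
- **What goes in the diary (Section 2.23).** "all participants will be asked to report any new or worsening problems that they perceive to be related to participation in activity and/or exercise", together with any relapses.
- **Active prompt (Section 2.23).** At fortnightly check-ins "the CI will overtly request any information regarding AE's". This sentence has no relatedness condition and names no arm.
- **Serious events (Section 2.23).** Any serious event, "whether thought to be related to any trial intervention or not, will be reported by the CI to the ST within 24 h" of the chief investigator (CI) learning of it. The TSC gives a second causality opinion when the CI and supervisory team think it unrelated.
- **Control arm (Section 2.22).** Usual care continues, and "with the exception of the trial assessments they will not be asked to attend any additional visits or sessions".
- **The diary elsewhere (Section 2.12).** Engagement with the home program "will be monitored based on exercise diary data recorded by the participant over the 12‐week program". Sections 2.13 and 2.17 add heart rate, perceived exertion and the exercises done. No separate control-arm diary is described.
- **Blinding (Section 2.21).** Neither the participants nor the CI, who collects the reports, is blinded.

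**The concern.** There are two weaknesses in how events enter the record.

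First, the diary request puts a causal judgment before the recording. A fall or dizzy spell that the participant puts down to Parkinson's or to medication lies outside the request, although an investigator might have judged it related to the program. Unblinded participants will also attribute differently by arm, because controls have no trial exercise to blame.

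Second, the prompt that could recover such events is tied to a fortnightly online contact that the control-arm description does not clearly accommodate.

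Safety is part of the first aim, and Section 2.25 allows early stopping for too many adverse events, a count that depends on how events are captured. Events not elicited during the 12 weeks cannot be reliably recovered later, and no analysis plan can repair that.

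**Working it through.** The document states no AE rate, capture share or AE comparison, so there is no figure to reproduce. The check is a comparison of the sections, followed by an illustration on assumed values.

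**1. Filter against later judgment.** Section 2.23 follows up those AEs that are considered related to the intervention. That presupposes a wider set of recorded AEs from which the related ones are picked. For serious events it states outright that reporting does not depend on relatedness, and it provides for judgment by the CI and supervisory team with a second opinion from the TSC. The diary request reverses this order, because the participant decides relatedness first. Section 2.14 describes diary recording of adverse effects and events with no such condition.

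**2. Prompting by arm.** Sections 2.14 and 2.23 place the prompt at a fortnightly drop-in or check-in (I take these to be the same contact). Over 12 weeks that is 12 / 2 = 6 contacts per participant. Section 2.22 gives controls nothing to attend beyond trial assessments. There are two readings:

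- The request to all participants includes controls. They then need a diary and a fortnightly contact, which no section describes for them.
- The contacts belong to the exercise program. Controls then have no stated prompt.

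The sections need reconciling under either reading.

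**3. Illustration of unequal prompting (all rates assumed).** Expected participants with a recorded AE = 12 × true risk × share captured. Take equal true risk in both arms and 90% capture in the exercise arm:

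| True risk | Exercise arm (90%) | Controls at 90% | Controls at 60% | Controls at 30% |
|---|---|---|---|---|
| 20% | 2.2 | 2.2 | 1.4 | 0.7 |
| 40% | 4.3 | 4.3 | 2.9 | 1.4 |
| 60% | 6.5 | 6.5 | 4.3 | 2.2 |

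The apparent ratio is 0.90/0.90 = 1.0, 0.90/0.60 = 1.5 or 0.90/0.30 = 3.0, whatever the true risk.

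**4. Illustration of the filter (all rates assumed).** Take a true risk of 40% among 12 participants, of whom a share f perceive their event as related, and suppose that the check-in recovers nothing. Expected count = 12 × 0.40 × f. P(none recorded) = (1 − 0.40 × f)^12.

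| f | Expected count | P(none recorded) |
|---|---|---|
| 100% | 4.8 | 0.002 |
| 75% | 3.6 | 0.014 |
| 50% | 2.4 | 0.069 |
| 25% | 1.2 | 0.282 |

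Any recovery at check-ins makes the loss smaller than shown. These tables give direction only and do not estimate the effect in this study.

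**The case against.** The other side has four fair arguments.

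- **The filter is not the whole intake.** Relapses are requested, the check-in asks for any AE information, and serious events are reportable regardless of cause. A reader might infer that only exercise-attributed events can ever be collected, or that the filter extends to serious events. The text supports neither. What remains is that the broader prompt helps only those who attend a check-in, and the diary request itself is still filtered.
- **No safety comparison is planned.** The objective in Table 1 is the safety of the program. Section 2.26.1 plans intervals against usual care for mechanistic, physiological and clinical outcomes, and the example progression criteria in Section 2.32 do not use AEs. A reader might infer that a planned between-arm AE analysis is biased, but none is described. The risk is to any by-arm description that may be made.
- **Drop-ins for the exercise arm only are an inference.** Section 2.23 speaks of all participants, and a remote check-in need not count as a visit or session. Section 2.10 has both groups instructed at a home visit, with details in another publication, and the timeline and pathway figures are not shown. So it cannot be said that controls have no contact, only that none is stated and that the sections fit poorly.
- **This is a feasibility study of 24 people, and an article condenses its protocol.** That tempers the weight of the point. It does not answer the diary rule, which the article states explicitly.

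**Conclusion.** The point holds in a limited form. The diary request applies a participant-attribution filter to the main safety measure. That sits badly with Section 2.14, with the relatedness judgments later in Section 2.23, and with unblinded reporting. As written, equal ascertainment in the two arms is not secured, because the unfiltered prompt has no stated control-arm route.

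The likely consequence is some under-recording of non-serious events, and possibly an artificial difference in any AE table by arm. The direction of that difference rests on one assumption, that capture is lower in controls. With equal capture there is no distortion. The size cannot be derived from the document, and no percentage-point bias should be quoted as a finding.

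**What to change.** 1. Reword the request in Section 2.23 so that both arms report all new or worsening health problems, including falls, whatever they think the cause. The investigators and TSC then assign relatedness, and events are reported both as all-cause and as related.
2. Reconcile Sections 2.14, 2.22 and 2.23. Either use the same brief remote prompt at the same interval in both arms, with a stated diary or form for controls, or state that safety is described for the exercise arm only.

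**Cost.** The rewording itself costs little. If controls do not already have the fortnightly contact, equal prompting adds up to 12 controls × 6 = 72 short remote contacts and slightly more attention to the control arm. The recorded AE count will rise, which should be expected when it is interpreted.

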### Roles and responsibilities

2.2

Research team:

The chief investigator (CI; author [name]) has overall responsibility for the implementation of this trial. The CI has lead responsibility for writing ethics submissions, developing training materials, and recruitment, and will be supported by three members of the supervisory team (ST; authors [name], [name], and [name]). The CI is also responsible for data analysis, participant liaison, online resources, and materials. One member of the ST ([name]) will be allocated to undertake postrandomization outcome assessments, blinded to trial arm allocation. Another member of the ST ([name]) who will not be involved in assessments will undertake randomization procedures.
Trial steering committee

This study will be overseen by an independent trial steering committee (TSC). The TSC will consist of one service user (PwP), and a practicing clinician. The TSC will provide ongoing guidance and advice on any conflict that arises within the research team. The TSC will receive three progress reports delivered by the CI throughout the course of the study.

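### The blinded outcome assessor belongs to the supervisory team that receives adverse event reports and helps judge withdrawal from HH4P, so the safety procedure as written conflicts with the blinding for the participants concerned

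*Protocol article*

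**What the plan says.** **Who is blinded, and until when.** Section 2.2 says that the chief investigator is "supported by three members of the supervisory team" (ST). One of these members "will be allocated to undertake postrandomization outcome assessments, blinded to trial arm allocation"; another performs the randomization. Section 2.21 repeats that the ST member "undertaking postintervention outcome assessments will be blinded to the participants' allocated group". It also sets the end point: "The final unblinding of the ST member who undertook assessments will be after the creation of a locked data set" and the analysis. The same section says that the chief investigator cannot be blinded.

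**Who handles safety.** Section 2.23 has the chief investigator ask about adverse events at fortnightly check-ins, and then: "These will then be recorded on the AE report form and reported by the CI to the ST". On whether an event should take a participant out of the HH4P programme, the section says: "It will be left to the judgment of the CI, ST, and TSC, whether or not an AE is of sufficient severity". Every serious adverse event goes to the ST within 24 h, and the chief investigator and ST make the first causality judgment. Section 2.25 gives any single ST member the power to end the research early on safety grounds. None of these sentences exempts the assessor.

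**Safeguards.** Section 2.21 promises: "Every effort will be made throughout to ensure these assessments are blinded". Its example is "by reminding participants not to discuss their group allocation with the blinded member of the ST". It also places baseline assessment before randomization, and holds assessments apart from intervention sessions and away from the home.

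**The concern.** The protocol gives one person two roles that conflict. As assessor, that ST member must not know a participant's arm until after lock and analysis. As an ST member, the same person receives safety reports from an unblinded colleague and shares in decisions that in some cases apply only to HIIT participants. The listed safeguards do not deal with information passing from the chief investigator to the ST, which section 2.23 requires.

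At stake is the credibility of post-intervention ratings, chiefly MDS-UPDRS part III, a rating scale with a clinician-completed component and a proposed primary outcome for the full trial (section 2.15). The study will use responsiveness to choose outcomes for that trial (Table 1, objective Bi) and will report 95% confidence intervals for the intervention effect (section 2.26.1). A blinding procedure that fails here could also be carried into the full trial, whose methods this study is meant to inform.

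**Working it through.** The protocol gives no figure to reproduce. The check is on roles, information flow and timing.

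1. **Same person.** Sections 2.2 and 2.21 both place the blinded assessor inside the ST. Section 2.23 addresses the ST without naming individuals, and section 2.25 extends the stopping power to each member. Read literally, the assessor is included.

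2. **Timing.** Adverse events are recorded and reported through the 12-week programme (sections 2.14 and 2.23). The second assessment visit is 24 h after the programme ends (section 2.10). The safety information therefore arrives before the ratings it could influence. Baseline assessments are unaffected because they precede randomization.

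3. **What each type of information reveals.**
   - *Judging withdrawal from HH4P:* only the intervention arm receives HH4P (sections 2.1 and 2.22), so the question arises only for a HIIT participant. The arm is revealed with certainty.
   - *Other adverse event reports:* all participants are asked to report problems that they link to activity or exercise. A report may point to HIIT through its content or the setting in which it arose, but it need not.
   - *Serious adverse events:* the first judgment is on relatedness to the trial. Both arms undergo the maximal exercise test at assessment visits (sections 2.10 and 2.15), so that judgment does not in itself identify the arm, although the details may.

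4. **Do the revealed cases still get assessed?** Yes, as far as possible. Section 2.19 seeks outcome data from all participants whether or not they adhered, for the intention-to-treat analysis. Someone taken out of HH4P should therefore still attend the post-intervention visit and be rated by the same assessor.

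5. **Weight of each affected rating.** Let *k* of the 12 HIIT participants (section 2.5) be rated by an assessor who knows their arm, and let *d* be the shift in each such rating. If all 12 are assessed, the HIIT arm mean, and so the arm difference, moves by *k* × *d* / 12:
   - *k* = 1: *d* / 12, about 0.08 *d*
   - *k* = 3: 3*d* / 12 = 0.25 *d*
   - *k* = 12: *d*, the ceiling

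   The document supplies neither *k* nor *d*. These lines show only the weight of each case and do not estimate bias.

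**The case against.** **It may be only an omission.** A journal article condenses a fuller protocol, and reporting lists, masked forms or recusal rules may be set out there. In section 2.23, ST may be shorthand for the appropriate members. Section 2.21 gives its reminder only as an example, so other measures may exist. This carries some weight, but the article does more than stay silent: it assigns the safety duties to the whole team and, in section 2.25, to any member. Where it means to separate ST roles it does so, as for the member who randomizes, who takes no part in assessments and is blinded to their results.

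**The extent is limited.** A reader might infer that any adverse event report unblinds the assessor, and hence that all HIIT participants are exposed. The text does not support that. Controls also report problems and are not barred from activity, nothing says that the report form states the arm, and section 2.23 rates the risk of adverse events as low. Whether the fortnightly check-ins include controls is unclear; if they do not, inference becomes easier.

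A reader might also infer that VO2max and the 30 s sit-to-stand test lose their blinding in the same way. VO2max is measured by gas analysis, and the article does not describe assessor influence on either test. Only MDS-UPDRS part III is plainly rater-scored.

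**The stakes are modest.** No formal test of treatment effect is planned, and the clinical outcomes are mainly descriptive. That lowers the consequence but does not reconcile the sections.

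**Conclusion.** The point holds in a limited form. Sections 2.2 and 2.21 cannot both be followed together with section 2.23 for any participant whose withdrawal from HH4P is put to the ST: the assessor learns that this person is in the HIIT arm before rating them. For other adverse event and serious adverse event reports, unblinding is possible or likely but not certain. The assessor is not thereby unblinded for the whole sample.

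The number of participants affected and the size of any bias cannot be derived from the document. The conclusion assumes that ST means all its members, as the wording suggests, and that no unpublished procedure exempts the assessor. Because it touches a proposed primary outcome and is easy to correct, it should be corrected.

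**What to change.** Reconcile sections 2.2, 2.21, 2.23 and 2.25 by stating that, until the data set is locked and analysed, the ST member who assesses outcomes:

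- receives no adverse event or serious adverse event reports;
- takes no part in causality, withdrawal or safety-stopping decisions.

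Those duties would rest with the chief investigator, the other ST members and the trial steering committee. Section 2.25 needs the same exception, or its reference to any ST member will reopen the gap. The change concerns only who receives information and takes part; it alters no criterion for withdrawal or stopping.

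The cost is a sentence or two of text and a changed distribution list, with no added staff. The downside is one fewer ST member in safety discussions.

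Optionally, the assessor could record a guess of allocation at each post-intervention visit, so that the success of blinding can be reported and inform the full trial. That is good practice and is not needed to remove the contradiction.
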